## Methods/design

### Design of the study

The study design is a two parallel group RCT stratified by sex, with 1:1 individual allocation comparing the Education Control condition and the Strongest Families Smart Website intervention (Intervention). Best practice guidelines for conducing RCTs will be followed in accordance with the CONsolidated standards of Reporting Trials statement (CONSORT), European International Conference on Harmonisation (ICH) Good Clinical Practice Guidelines, and Tri-Council Policy Statement: Ethical Conduct for Research Involving Humans (trial registry: ClinicalTrials.gov # NCT01750996).

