Those participants with a child meeting the screening inclusion criteria are enrolled in the next phase of the study. The study staff complete a recruitment telephone call introducing the study in more detail and screening for eligibility. During this telephone call, if the participant expresses their preliminary interest in participation, they are registered in the Smart Website electronic platform called IRIS (Intelligent Research and Intervention Software). If the participant declines to participate or is ineligible for the study, a record of this is entered into the system. If recruitment is successful, the data submitted by study staff generates an automated email trigger from IRIS to the participant containing instructions to set up a password for IRIS. On first login, the participating parents are presented with the online consent form. A separate consent telephone call with the parents is scheduled a few days after the recruitment telephone call. During the consent telephone call, the staff confirms the parents’ online consent, and, if consent is provided, the online baseline measures in IRIS are released to be completed by the participating parent. Once the online baseline questionnaires are completed, IRIS sends a task prompt to the study staff to complete the randomization process.

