#### Sample size

As per Cohen’s [59] suggestion that standardized effect sizes of 0.20, 0.50 and 0.80 be considered as small (detectable), medium and large, respectively, we expect to observe medium to small incremental effects in the order of 0.30 to 0.35 standard units between the intervention and control groups, accounting for multiple comparisons using hierarchical linear modelling (HLM) analysis. This would require 250 participants per group for the trial, allowing for 30% attrition over time. It is expected that adding data from one year follow-up will increase the power to detect differences. An alpha of 0.05 was chosen on an *a priori* basis for the statistical analyses in order to decrease the probability of type II errors.

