### Measures

The child and parent applicable measures are completed online using secured access to the Strongest Families Smart Website intervention. The teachers are asked to complete the SDQ and TRF on paper and submit the completed questionnaires to the study team. With the exception of the screening measure, all post-screening measures are administered at baseline, at 6 months and at 12 month follow-up.

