### Data management and analysis

#### Statistical analyses

Latent growth analysis, mixed effects regression, structured covariance analysis, or hierarchical linear modeling (HLM) will be used. The primary analysis will model the pattern of differences between the groups using growth curve analysis and the statistical software MLwinN [88]. With the primary outcome of CBCL externalizing scores, the analysis will treat repeated measures within individuals as Level 1, and differences in the coefficients between the Strongest Families Smart Website intervention and Education Control conditions as Level 2. In effect, the approach will be to estimate parameters of growth (i.e., the slope of the outcome scores over time) for each individual, and compare these between the Strongest Families Smart Website intervention and Education Control conditions. In addition to comparing trajectories of response among children allocated to the two arms of the trial, net differences in response will be estimated by transposing the intercept to the end of the trial [89]. This will allow a formal test of outcome differences. In addition, aggregate anonymous analysis of the characteristics of eligible children whose families did not consent to participate in the trial will be conducted. This will be important in understanding to whom the results of the trial can be generalized. The next step will be to test the possible moderating influence of program utilization using tracking reports of website activities (e.g., time on task, number of screens viewed, sessions completed).

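### The planned growth model, on its natural reading, lets each arm have its own baseline level, so both stated tests of the primary outcome are valid but less precise than a model with a common baseline mean

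*Protocol article*

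**What the plan says.** The Statistical analyses section names growth curve analysis of CBCL Externalizing as the primary analysis. On the data structure it says that "the analysis will treat repeated measures within individuals as Level 1", with arm differences in the growth coefficients at Level 2. The Measures section states that "all post-screening measures are administered at baseline, at 6 months and at 12 month follow-up", so baseline is one of those repeated outcomes.

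Two arm comparisons follow. The first compares individual slopes. The second is additional: "net differences in response will be estimated by transposing the intercept to the end of the trial". The article describes this second comparison as giving a formal test of outcome differences. Baseline CBCL is not named as a covariate, and no common baseline mean is stated.

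Baseline is taken before allocation. Under Screening and inclusion criteria: "Once the online baseline questionnaires are completed, IRIS sends a task prompt to the study staff to complete the randomization process". The Sample size section expects effects "in the order of 0.30 to 0.35 standard units between the intervention and control groups" and states: "This would require 250 participants per group for the trial, allowing for 30% attrition over time".

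**The concern.** Because baseline questionnaires are completed before allocation, any difference between arms in baseline CBCL is due to chance. A model that gives each arm its own baseline level estimates that chance difference as if it might be real.

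Moving the intercept to 12 months then gives baseline almost no weight in the arm comparison, so the test is close to a comparison of final scores. The slope comparison goes the other way and subtracts baseline in full, as a change score does. Neither uses baseline at the weight that minimizes variance. At stake is the precision of the primary result, with data that the trial collects in any case.

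**Working it through.** **The plan's own figure.** Take a two-sided alpha of 0.05 (sidedness is not stated), 80% power (also not stated), and an effect of 0.30 SD. Then n per arm = 2(1.960 + 0.842)²/0.30² = 174.4, so 175, and 175/0.70 = 250. This reproduces the stated 250 per group as a plain two-sample comparison with no baseline term. An effect of 0.35 SD with 90% power also comes close: 172 per arm, or 246 after inflation.

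**Why free baselines are the natural reading.** If the arms share a baseline mean and growth is linear, the 12-month difference equals 12 times the monthly slope difference, and the two tests are the same test. A second test in addition to the slope comparison makes sense only if each arm has its own starting level. This is an inference; the article does not state it.

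**Complete data.** Visits are at 0, 6 and 12 months, each score has SD 1, and any two visits correlate r (compound symmetry). The article does not give r; 0.4 to 0.7 is assumed. Variances are relative to the raw final score.

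- End-of-trial intercept, free baselines: visit weights (−1/6, 1/3, 5/6), variance (5 + r)/6.
- 12-month change from the slope: variance 2(1 − r).
- Same linear model with a common baseline mean: the free-baseline intercepts at 0 and 12 months each have variance (5 + r)/6 and covariance (7r − 1)/6, so the variance is (5 + r)/6 − [(7r − 1)/6]² / [(5 + r)/6].
- Visit-specific model with a common baseline mean, or baseline as covariate: 1 − r².

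| r | Intercept test | Slope test | Common-baseline growth | Visit-specific |
|---|---|---|---|---|
| 0.4 | 0.900 | 1.200 | 0.800 | 0.840 |
| 0.5 | 0.917 | 1.000 | 0.727 | 0.750 |
| 0.6 | 0.933 | 0.800 | 0.629 | 0.640 |
| 0.7 | 0.950 | 0.600 | 0.505 | 0.510 |

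Example at r = 0.6: 5.6/6 − (3.2/6)²/(5.6/6) = 0.933 − 0.305 = 0.629. If correlation decays with time, the intercept test rises to 0.96–0.99 of the final-score variance.

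**With the planned attrition.** Start from 250 per arm. The article gives 30% attrition in total; assume 15% of those randomized are lost before each follow-up visit. Then 70% have all three visits, 15% have baseline and 6 months, and 15% have baseline only. Generalized least squares on these patterns gives a variance factor k, and power = Φ(0.30/√(2k/250) − 1.96).

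| r | Intercept: k, power | Slope: k, power | Common-baseline growth: k, power | Visit-specific: k, power |
|---|---|---|---|---|
| 0.4 | 1.174, 87.2% | 1.527, 77.5% | 1.087, 89.6% | 1.183, 87.0% |
| 0.5 | 1.162, 87.5% | 1.288, 84.0% | 0.988, 92.1% | 1.050, 90.5% |
| 0.6 | 1.142, 88.1% | 1.042, 90.8% | 0.853, 95.3% | 0.892, 94.4% |
| 0.7 | 1.116, 88.8% | 0.790, 96.5% | 0.685, 98.2% | 0.707, 97.9% |

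Example at r = 0.6, intercept test: √(2 × 1.142/250) = 0.0956; 0.30/0.0956 − 1.96 = 1.18; power 88.1%.

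The common-baseline growth model beats both stated tests in every row. Over the intercept test it gains 2.4, 4.6, 7.2 and 9.4 points; over the slope test 12.1, 8.1, 4.5 and 1.7 points.

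**The case against.** **Free baselines are not stated.** The section lists several model families joined by *or*, and a condensed article commonly leaves covariates and constraints to a fuller plan. This stands as a caution. It does not dispose of the point, because the section fixes a level structure and a formal test that make sense together only with free baselines. The objection is to that stated analysis and not to missing detail.

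**The intercept test is additional, and the slope test already uses baseline.** True, and at r = 0.7 the slope test comes within 2 points of the common-baseline model. At r = 0.4, however, it is the weakest of the four, and the article does not say which of its two tests prevails.

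**The gain may be small.** This stands. With attrition, the visit-specific model gains nothing over the intercept test at r = 0.4. The documents give no correlation from baseline to 12 months. Selecting children with an SDQ Conduct score of 5 or more may lower it, and the Background says that only about half of aggressive preschoolers go on to persistent problems. The quoted test-retest reliability of 0.81 is at best a ceiling. Nothing shown establishes that the score tracks strongly over a year.

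**Stronger readings to avoid.** A reader might infer that the planned test is biased or invalid; it is neither under randomization. A reader might infer that the trial is underpowered; the intercept test exceeds 80% power at 0.30 SD throughout. A reader might also take the complete-case contrast at r = 0.6 as the cost: 0.933/0.640 = 1.46, or 46% more children, and about 11 points of power at 175 per arm. That ignores the partial data a mixed model uses. With planned attrition, the visit-specific gain at r = 0.6 is about 6 points.

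**Conclusion.** The point holds as a loss of precision. On the natural reading of the Statistical analyses section, both stated tests of the primary outcome use a baseline measured before randomization less well than they could. Power at 0.30 SD is about 87–89% for the intercept test and 78–97% for the slope test, against 90–98% for the same growth model with a common baseline mean.

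These figures rest on assumptions that the article does not supply: visit correlations of 0.4 to 0.7 under compound symmetry, a two-sided alpha of 0.05, and attrition split evenly over the two follow-up intervals. Under decaying correlations (0.5 to 0.7 between baseline and 12 months) the pattern is the same: 86–88% for the intercept test and 92–98% with the common baseline. The direction held at every correlation tried from 0.3 to 0.8, with and without dropout; the size depends heavily on the correlation.

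**What to change.** Keep the growth model and constrain the arms to a common baseline mean: no arm effect at time 0, and an arm-by-time term only. Report the resulting 12-month difference as the single formal test, which also settles which of the two present comparisons prevails.

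The linear version makes the 6-month difference half the 12-month difference. If that is not credible, use arm-by-post-baseline-visit terms with a common baseline mean, or enter baseline CBCL Externalizing as a covariate with a separate coefficient at each visit. That version gives about 87–98% power over the same range, with no gain over the intercept test at r = 0.4.

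The cost is a change of model wording. No new data are needed, no family is affected, and a multilevel model of the kind already planned can carry the constraint. If an analysis plan already contains it, the published description needs only to say so.

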### Study goals

The goal of the research program is to translate and replicate the Strongest Families™ telephone-based program in a Finnish population trial using a Smart Website delivery system. A population-based randomized controlled trial (RCT) is currently being conducted with 4 year-old children displaying disruptive behaviour. Specific objectives of the SFFC Smart Website intervention research program are to:

(1) develop a collaborative network that builds partnerships among investigators that will inform the content of our existing program by harnessing the advances of technology to customize care using videos, audio-clips and written exercises that demonstrate skill implementation;

(2) develop methods for early identification of challenging behaviour in primary health care in Finland;

(3) evaluate the prevalence of early signs of disruptive behaviour in Finnish 4 year-old children;

(4) develop the Strongest Families Smart Website intervention based on the Strongest Families telephone-based program [38] for the prevention and treatment of disruptive behaviour in 4 year-old children;

(5) evaluate the effectiveness of the Strongest Families Smart Website intervention for the early identification and treatment of disruptive behaviour in 4 year-old children, compared to an Education Control condition; and

(6) examine the possible moderating influence of program utilization using tracking reports of website activities (e.g., time on task, number of screens viewed, sessions completed).

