#### Randomization

The two randomization sequences (i.e., sex stratification) are generated with a 1:1 ratio (i.e., intervention versus Education Control condition) using a computerized random permuted block sequence generator (Random Allocation Software [60]) with concealed block sizes to ensure study staff blinding. A sequential, double envelope system is utilized to conceal individual placement. The sequential envelopes are labeled and colour-coded according to sex. The delegated study staff complete randomization by selecting the next sequential envelope per applicable stratification, affix the sticker that reveals the condition placement on the participant’s source document and enter the group placement information into IRIS. The next study steps released by IRIS are dependent on the group placement entered; IRIS unlocks the appropriate user interface (i.e., Strongest Families Smart Website intervention with weekly telephone coaching-Intervention condition; Static website with parenting tips-Education Control condition). After randomization, the participants receive an email informing them of the randomization results and a link to the relevant website. In addition, the participants are not restricted from seeking other assistance for problems that they encounter.

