#### Education control condition

The participants randomized to the Education Control condition receive access to a static website with parenting tips as well as a single 45-minute telephone call with a coach reviewing the parenting tips. The Education Control was chosen as the Control condition as opposed to a waitlist control or standard care for the following reasons: (1) a waitlist control condition does not allow for a long-term follow-up, (2) for the majority of families in the Finnish population, standard care constitutes no care at all, and (3) the Education control was deemed as an ethical alternative for parents with a challenging child.

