#### Intervention condition

The participants randomized to the Intervention condition receive a Smart Internet version of the Strongest Families telephone-based program [38,61,62], an 11-session, evidence-based parenting program, that focuses on skills for strengthening parent–child relationships; reinforcing positive behaviour; reducing conflict; managing daily transitions; planning for potentially problematic situations; and promoting pro-social behaviour. The Strongest Families telephone-based program was initially designed to target 3–12 year-old children. For the current study, the program content was modified into a web-based format and in accordance with the developmental level of 4 year-old children. Minor culturally appropriate changes were made throughout the program to accommodate for issues such as differences in the schooling and daycare systems between Finland and Canada.

The participating parents are asked to complete the 11 Strongest Families sessions online. The participants are encouraged to complete one session per week and at times most suitable to their daily life using a computer with an internet connection. Only one parent is the active participant during the program; however, the participant is encouraged to share the program content with the other partner when possible. The child does not take part in the telephone calls or use the website. The participant works through the online material for each session including exercises, instructional videos and skill demonstration audio and video clips. During the sessions, the participants are required to complete specific knowledge-based and experience-related questions. The participants are encouraged to complete each session in approximately one week after which the session concludes with a weekly telephone call with a trained coach (with health care professional certification) who provides support, responds to participants’ questions and reviews successful implementation of the program skills. If session skill adoption is considered adequate based on the coach’s professional experience, the next session is introduced at the end of the telephone call. Otherwise, the participant is encouraged to spend additional time with session content to acquire a necessary skill level.

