##### Program utilization measure

Each participant’s time on the website is downloaded using appropriate time-out values and the percentage of primary screens the participants observed. Program satisfaction and therapeutic alliance questions are released at the end of treatment for the intervention group only. Program satisfaction is also measured at 12 months.

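### Program utilization is to be tested as a moderator, but it arises after randomisation and has no comparable control-arm measure, so the test cannot show effect modification

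*Protocol article*

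**What the plan says.** The last of the six objectives in the protocol article (Study goals) is to "examine the possible moderating influence of program utilization using tracking reports of website activities". The Statistical analyses section repeats it as a step after the primary model: "The next step will be to test the possible moderating influence of program utilization using tracking reports of website activities". Both places give time on task, number of screens viewed and sessions completed as examples.

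The Program utilization measure section comes directly after the parent ADHD scale, under the Moderator measure heading. It says: "Each participant’s time on the website is downloaded using appropriate time-out values and the percentage of primary screens the participants observed". The next sentence restricts other items to one arm: "Program satisfaction and therapeutic alliance questions are released at the end of treatment for the intervention group only".

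On timing, the Randomization section says: "After randomization, the participants receive an email informing them of the randomization results and a link to the relevant website". On content, the two arms differ:
- Intervention condition: "The participating parents are asked to complete the 11 Strongest Families sessions online".
- Education control condition: participants "receive access to a static website with parenting tips as well as a single 45-minute telephone call with a coach".

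**The concern.** A moderator analysis asks whether the treatment effect differs between kinds of family. The grouping variable must therefore be fixed before treatment can influence it, and must mean the same in both arms. Parent ADHD symptoms can meet that requirement. Website usage cannot: it is part of what happens to a family after allocation, and the two websites offer different things to use.

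What can still be estimated is an association between usage and outcome among families given the programme. Families who use it more may differ from the start, and usage may itself respond to how the child and parent are doing. If such an association is reported as moderation, readers may take it as evidence on how much use is needed for benefit. The Discussion expects the trial to show how the intervention functions and can be improved and disseminated, so the label bears on one of the trial's stated uses.

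**Working it through.** **1. Is utilization a baseline variable?** No. The link to the website is sent only after randomisation, so time, screens and sessions are all post-randomisation.

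**2. Is there a comparable control measure?**

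| Metric | Intervention | Education control |
|---|---|---|
| Sessions completed | 0 to 11 | Not defined |
| Screens viewed | Screens of an interactive, personalised programme | At most, pages of a static tips site |
| Time on task | Time working through sessions | At most, time reading tips |

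The first row has no control value. The other two could be logged for controls, but would measure something else. A product term of arm and usage would compare unlike quantities.

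**3. What drives usage within the intervention arm?** The Intervention condition section has the coach introduce the next session only when skill adoption is judged adequate; otherwise the parent is encouraged to spend longer on the current one. The components section says that infrequent visitors are prompted. Two consequences follow:
- Sessions completed partly records early response, which favours a positive association with improvement.
- Time on task can be higher in families who are struggling, which favours a negative one.

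**4. How many families would be analysed?** The Sample size section gives 250 per group with 30% attrition: 250 × 0.70 = 175. That design figure reproduces. A standardised difference of 0.30 at two-sided alpha 0.05 needs 175 per group for 80% power (the power is assumed; the article states none), and 175 / 0.70 = 250.

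**5. How often would selection alone give a significant result?** Assume no treatment effect and a usage-outcome correlation r produced entirely by selection. By Fisher's z with n = 175, the probability of significance is approximately Φ(atanh(r) × √(n − 3) − 1.96), with √172 = 13.115.

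| r (assumed) | atanh(r) × 13.115 | Probability significant |
|---|---|---|
| 0.10 | 1.316 | 26% |
| 0.20 | 2.659 | 76% |
| 0.30 | 4.059 | 98% |

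**6. How strong must selection be?** Suppose one latent family trait has correlation c with usage and the same correlation c with improvement. The induced r is then c². An r of 0.20 needs c = √0.20 = 0.45, and an r of 0.30 needs c = 0.55. A simulation of this set-up (4,000 replicates, 175 families, zero effect) gave these rates of significance:

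| c (assumed) | Induced r = c² | Significant |
|---|---|---|
| 0 | 0 | 5% |
| 0.2 | 0.04 | 8% |
| 0.3 | 0.09 | 23% |
| 0.4 | 0.16 | 55% |
| 0.5 | 0.25 | 91% |

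At c = 0.5, above-median users looked about 0.20 SD better than controls and below-median users about 0.20 SD worse, although the true effect was zero.

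**The case against.** The strongest reply is that this is a matter of terminology in a late, subordinate analysis. Utilization appears in neither the primary nor the secondary hypothesis. The text speaks only of a possible influence, and the model, analysis set and covariates may be set out in a document not shown. That is fair as far as it goes, and the absence of those details is not criticised here. But the estimand and the variable are fixed in the article, in the objectives and again in the analysis section. Further model detail would not turn this variable into a moderator.

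Four stronger readings are tempting and not supported:
- *Utilization exists only in the intervention arm.* This is certain only for sessions. The measure is worded for each participant, both arms have a website, and the next sentence marks an arm restriction where one was meant. The supportable statement is that no comparable measure exists in the control arm.
- *The trial will report that more use brings more benefit.* The article makes no dose or causal claim, and the time-on-task mechanism in step 3 could push the other way.
- *The article itself admits that income, education, stress and depression confound use of this programme.* The Background sentence on these traits concerns traditional parent training. Confounding here is plausible but not conceded.
- *A false positive is likely.* The 76% and 98% rest on correlations with no source in the document. Weaker selection gives rates nearer the nominal 5%.

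**Conclusion.** The point holds, with limited reach. Testing utilization as a moderator, as objective 6 and the Statistical analyses section propose, cannot identify effect modification: the variable is post-randomisation and has no like-for-like control measure. What is left is a non-randomised association open to self-selection and reverse causation, in a direction that may depend on the metric.

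The size is illustrative. With 175 intervention families and no treatment effect, an assumed selection-only correlation of 0.20 is significant about 76% of the time, falling to 26% at 0.10. These figures assume a two-sided 0.05 test, 30% attrition in the intervention arm and a simple correlation analysis. The randomised primary comparison and the 250 per group are untouched. The change should be made because it costs almost nothing and alters what the trial may conclude about usage.

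**What to change.** In objective 6 and in the Statistical analyses section, replace the moderation wording with an exploratory, non-randomised association between usage and outcome within the intervention arm, stated to be non-causal. Adjust for baseline covariates already collected (for example socioeconomic status, parental education, DASS-21 and baseline CBCL), and report each usage metric separately. Adjustment reduces measured confounding but does not remove reverse causation, and the text should say so. Keep the term moderator for baseline variables such as the parent ADHD score, and place the utilization measure under a heading of its own.

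If an effect of receiving the programme is wanted, add as a supplement a complier-average estimate that uses randomisation as the instrument. The threshold should be low, such as any session started, so that it is plausible that families below it gain nothing from allocation. At an all-11-sessions threshold that assumption would fail if partial users benefit, and the estimate would be biased upward. Higher thresholds belong in sensitivity analyses only, with the assumptions stated.

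The cost is a change of wording and, if the supplement is taken up, one further model. No new data are needed. The downside is a weaker claim about usage and, for the complier estimate, wider intervals.

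The article reports recruitment still under way in August 2013 and one-year follow-up to be completed in 2015, so on that timetable the change could be specified before the final outcome analysis.
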